#### Sample size

As this proposed study is to develop and evaluate the feasibility, acceptability, and preliminary effectiveness of the PPI intervention, a widely acceptable sample size (i.e., 30 participants in each study group) for a preliminary analysis to examine intervention feasibility and to estimate a between-group effect will be adopted [22]. Considering a 20% attrition rate, 36 people with SCI per study group (i.e., 72 people in total) will be recruited. A purposive sampling by key informants (containing both participants who completed the whole intervention sessions and those who withdrew from the intervention period) will be conducted for focus-group interviews (i.e., 4-5 participants per group), until saturation of the information was reached.

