#### Randomization and masking

After the completion of the baseline assessment, eligible participants will be randomly allocated to two study groups. The random allocation will be conducted by an independent researcher with an external randomization service (i.e., sealedenvelope.com), using random permuted block sizes (i.e., 4 or 6) to ensure balanced group numbers. Participants will not be blinded due to the nature of the intervention. Participants will be reminded to keep the intervention content confidential and not discuss this with participants in the control group to avoid contamination. Assessor-blind is not adopted as measurements are self-reported. Assistance provided by caregivers and research assistants might be needed for those who have difficulties in filling out surveys.

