employment, marital status, ethnicity, cause, level of injury, and time since the injury. The following outcomes/instruments will be used to assess the preliminary effects of the PPI intervention. Effect sizes (e.g., Cohen's d) and confidential intervals will be calculated to estimate the sample size for a future fully powered randomized controlled trial.

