## Data analysis

All quantitative data from the pre- and post-tests will be numerically coded, summarized (with descriptive statistics), and analyzed using IBM SPSS 26. Both intention-to-treat and per-protocol analyses will be performed. Effect sizes of between-group comparisons will be estimated using Cohen's *d* which is applicable for small sample sizes [29]. Comparison of baseline information between two study groups will be performed by t-test, Mann-Whitney U, and/or Chi-square tests depending on the nature of the data. The generalized estimating equation will be used to assess the changes in the outcome measurements between groups over time, followed by contrast tests. Co-variance (if any found in the baseline comparison) will be adjusted during the analysis of intervention effects. Subgroup analysis will be conducted for certain factors (e.g., complete and incomplete injury or intervention completion and non-completion). Level of significance is set at  $p < 0.05$  (2-tailed).

Focus group interview data will be content analyzed. Tape-recorded interviews will be transcribed into Cantonese by one research assistant and cross-checked by the other research assistant. Codes will be discussed and agreed between our team members, combined to form categories/subcategories, and explained with verbatim data. Any discrepancy in coding/category will be discussed and final themes/subthemes will be confirmed by our team.

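### Covariates are picked by baseline significance tests between randomised arms, so the adjustment follows chance imbalance rather than prognosis and gives up precision

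*Protocol*

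**What the plan says.** Three sentences in the protocol's Data analysis section bear on this.

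- Baseline testing: "Comparison of baseline information between two study groups will be performed by t-test, Mann-Whitney U, and/or Chi-square tests depending on the nature of the data".
- Outcome model: "The generalized estimating equation will be used to assess the changes in the outcome measurements between groups over time, followed by contrast tests".
- Covariate rule: "Co-variance (if any found in the baseline comparison) will be adjusted during the analysis of intervention effects".

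The section closes with "Level of significance is set at" 0.05, two-sided, and gives no separate level for the baseline tests. I therefore read a covariate as found when its baseline test reaches p < 0.05.

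No covariate is named in advance. The design supplies none either: Randomization and masking describes allocation "using random permuted block sizes (i.e., 4 or 6) to ensure balanced group numbers" and states no stratification factor. The characteristics recorded at baseline are listed under Preliminary effectiveness: age and gender, then "employment, marital status, ethnicity, cause, level of injury, and time since the injury". That makes eight. There are three primary and three secondary outcomes.

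**The concern.** Randomisation makes the null hypothesis of a baseline test true by construction, so the test answers no useful question. Used as a gate for covariates it has two faults. It admits variables because they happened to differ, whether or not they predict the outcome. It also shuts out strong predictors that happened to be balanced or only moderately imbalanced. The variable most likely to predict a follow-up score, the same score at baseline, would qualify as a covariate in only about one trial in twenty.

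The between-group effects and their intervals are meant to inform the size of a later full trial, and tests at 0.05 are planned. With about 30 evaluable participants per arm, precision is scarce, and a model whose terms depend on the draw is harder to interpret.

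**Working it through.** **Inputs from the protocol.** Evaluable "30 participants in each study group"; 36 per arm recruited; alpha 0.05 two-sided; eight listed characteristics; six outcomes; assessments at baseline, post-intervention and 3 months. **Assumed, because the protocol gives no value:** the baseline to follow-up correlation rho (range 0.3 to 0.8), a true effect of 0.5 SD for the power figures, independent baseline tests, and complete data.

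**The plan's own figure.** 30 × (1 + 0.20) = 36 per arm, 72 in total, as stated. Nothing below turns on how attrition was applied.

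**Step 1: chance of at least one flag.** 1 − 0.95^k for k independent tests.

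- k = 8 (listed characteristics): 1 − 0.95^8 = 0.34; expected flags 8 × 0.05 = 0.4.
- k = 14 (adding six outcome baselines): 1 − 0.95^14 = 0.51; expected flags 14 × 0.05 = 0.7.

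**Step 2: smallest observed imbalance that is flagged.** For a t-test, in SD units, this is t(0.975; 2n − 2) × √(2/n).

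- n = 36: 0.47 SD.
- n = 30: 0.52 SD.

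An observed 0.3 SD at 36 per arm gives t = 0.3/√(2/36) = 1.27, p = 0.21, so the rule leaves it unadjusted every time.

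**Step 3: precision.** Variance of the treatment contrast, relative to comparing follow-up values alone:

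| rho | change contrast, 2(1 − rho) | adjusted for own baseline, 1 − rho² | ratio, (1 + rho)/2 |
|---|---|---|---|
| 0.3 | 1.40 | 0.91 | 0.65 |
| 0.5 | 1.00 | 0.75 | 0.75 |
| 0.7 | 0.60 | 0.51 | 0.85 |
| 0.8 | 0.40 | 0.36 | 0.90 |

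The ratio follows from (1 − rho²)/[2(1 − rho)] = (1 + rho)/2. At rho 0.5 and 0.7 the variance falls by 25% and 15%. A change contrast would need 1/0.75 = 1.33 or 1/0.85 = 1.18 times the participants to match.

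**Step 4: the rule as a whole.** Simulation with 40,000 trials per setting, 30 per arm, normal outcome with SD 1. The rule adjusts for the outcome's baseline only when its t-test gives p < 0.05; otherwise it uses either the change contrast or the follow-up comparison. Rho runs from 0.3 to 0.8.

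- Baseline flagged: about 5% of trials.
- Overall type I error under the rule: 0.042 to 0.046 (change contrast) or 0.031 to 0.049 (follow-up comparison). With fixed baseline adjustment: 0.048 to 0.051.
- Among trials with baseline p between 0.05 and 0.20, where the rule does nothing: the estimate is off by 0.08 to 0.28 SD (change contrast, against the direction of the imbalance) or 0.12 to 0.32 SD (follow-up comparison, in its direction). Type I error there is 0.06 to 0.13. Fixed adjustment gives about zero bias and about 0.05.
- Power at an effect of 0.5 SD, rho 0.5: 0.58 with fixed adjustment, 0.48 under the rule on either version. At rho 0.7: 0.76 against 0.70 (change contrast) or 0.49 (follow-up comparison).

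**The case against.** **The GEE already handles baseline.** This largely stands. A model for changes over time with a pre-intervention assessment most naturally takes baseline as a repeated response. A reader might infer that baseline is ignored unless it happens to differ; the text does not support that. What remains is that a change contrast is less precise than baseline adjustment at every rho below 1.

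**Model detail belongs in the SAP.** Also fair: silence on how baseline enters the GEE would not be a finding by itself. The covariate rule, however, is stated in the protocol, and it is the rule that is at fault.

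**Type I error and intervals.** A reader might infer that data-driven selection inflates type I error or makes the intervals too narrow. In the simulation the rule is slightly conservative overall. The excess appears only conditional on a moderate, unflagged imbalance.

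**Low power of the baseline tests.** A reader might also argue that the tests lack power to detect a real imbalance. Randomisation rules out a population difference, so power is the wrong measure. The relevant quantity is the threshold in step 2.

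**The count of tests.** The protocol speaks only of baseline information and does not say that outcome baselines are tested, so 34% is the better-grounded figure. Both figures assume independence.

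**It is a pilot.** Feasibility and acceptability come first among its aims, and the protocol does not say that the Cohen's d used for planning comes from the adjusted GEE. That limits the importance of the point but does not remove it.

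**Conclusion.** The concern holds as a fault in a stated rule. Covariates chosen by baseline tests follow chance. Some covariate would be selected in about a third of trials from the listed characteristics alone (about half if outcome baselines are included), while observed imbalances below roughly half an SD go unadjusted whatever their prognostic weight. Against the likely change contrast, the avoidable loss is 15% to 25% of the variance at rho 0.7 to 0.5. These sizes rest on independent tests, t-test thresholds, complete data and an assumed rho. The harm is to precision and to validity given the imbalance actually seen; randomisation still protects the unconditional comparison. For a pilot this is worth correcting but is not a fatal flaw.

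**What to change.** In Data analysis:

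1. Replace the baseline tests with a description of baseline by arm.
2. Delete the rule that adjusts for whatever the baseline comparison finds.
3. State that each post-intervention and 3-month outcome is analysed with its own baseline value as a covariate, with the follow-up values as the GEE responses.
4. Name any further covariate in advance on prognostic grounds. Injury completeness is a candidate: eligibility depends on it and the plan already names it as a subgroup factor. The protocol links injury severity to inactivity, but makes no such case for depression or pain.
5. Label all other adjustment as sensitivity analysis.

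For the questionnaire outcomes the cost is wording only, because baseline values are collected before allocation. The Fitbit outcome needs a check. The tracker is worn throughout the study, but no wear period before randomisation is stated, and the pre-intervention test is described as questionnaires. Baseline adjustment for that outcome applies only where a pre-randomisation value exists, and the protocol should say whether one will.

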### (iii) Interventions

The Intervention Group--The eight-week Physical-Psychological Integrative online-group intervention

Part I: Physical exercise. A guiding video of performing exercises was specifically developed for the SCI population by two experienced physiotherapists in Hong Kong. The video mainly includes warm-up, mobilization, strength exercises, aerobic exercises, and cool-down sessions.

Part II: An eight-week online intervention. The PPI intervention includes eight weekly online groups (with 4-5 participants in a group) sessions (with each session lasting for 60-90 minutes). At the beginning of each online group meeting, the intervention provider will use motivational interviewing techniques [23] to promote participants' adherence to the physical activity program mentioned in Part I, followed by online group psychological intervention. The content of the intervention will be adapted from the mindfulness-based stress reduction proposed by Kabat Zinn (1992), practice guideline of 'mindfulness for health' to relieve pain, reduce stress, and restore well-being [24]. The content of the intervention includes eight themes/sessions (the details of the intervention content are shown in Appendix 2): Session 1- Orientation and engagement; Session 2- Awareness and Acceptance; Session 3- Non-judgement; Session 4- Stay present and let go; Session 5- Our thoughts are not real & Response without reacting; Session 6- Empowerment of self-management and discuss pain management; Session 7- Seek out pleasant things and social support; Session 8- Review the intervention and end the programme. Two audio-tape recorded sessions (i.e., 20 minutes each) of mindfulness practice will be given to the participants for their daily practice. The intervention will be carried out by an experienced social worker trained in psychology, motivational interviewing, and mindfulness-based stress reduction.

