### The control group

Participants in the control group will receive a video call (approximately 60 minutes each week for eight weeks) from the trained research assistant with psychological background, i.e., to provide general physical and psychological suggestions (e.g., encouragement of performing physical activities, and communication skills with family members/friends, and engagement in the community life). This is to control the contact effects of the PPI intervention.

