### Ethical considerations

Ethical approval will be obtained from the Hong Kong Polytechnic University. This study will be performed in accordance with the Helsinki Declaration. Written informed consent will be obtained from all participants before the baseline assessments of the study, and will also be obtained from purposely sampled participants prior to all focus-group interviews. Participation is entirely voluntary for people with SCI and they can withdraw from the research at any time without any penalty. Participants' identities and data (information

collected and videotape records) will be protected by maintaining anonymity and confidentiality. Only authorized personnel can access the data for analysis.

(iv) Data processing and analysis

Feasibility and acceptability

**The feasibility** assessment of subject recruitment and follow-up will include (1) time taken to recruit the target sample size; (2) recruitment rate: the number of eligible participants approached who agree to consent divided by all subjects eligible to participate; (3) retention rate: the number of participants who complete the study divided by all participants who agree to consent; (4) drop-out rate: the number of participants who dropped out after randomization divided by all participants who agree to consent; and (5) reasons for dropping out will be collected from participants who dropped out.

**The acceptability** of the intervention will be indicated by (1) adherence rate: the number of PPI intervention sessions practiced divided by the total number of required sessions; (2) adverse events record associated with PPI intervention; and (3) satisfaction: participants' satisfaction with the intervention will be assessed with the Client Satisfaction Questionnaire [25]. The acceptability of the intervention will also be assessed by focus-group interviews with a purposive sample of participants who completed the whole intervention sessions and those who withdrew from the intervention period. Participants' perspectives about the acceptability, strengths, and limitations of the study and suggestions on the improvements of the interventions will be explored.

Preliminary effectiveness

All participants will be assessed at pre-, post-intervention, and 3-month follow-up by the research assistant. A self-designed form will be used to collect data on participants' socio-demographics and medical history, including age, gender,

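### Intervention completion is listed as a subgroup factor although it arises after randomisation, so an arm comparison within its levels is not randomised and is liable to bias of unknown sign

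*Protocol*

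**What the plan says.** The Data analysis section names two example factors in one sentence: "Subgroup analysis will be conducted for certain factors (e.g., complete and incomplete injury or intervention completion and non-completion". The same section sets a two-sided 5% significance level and does not mark the completion split as exploratory, descriptive or non-randomised.

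The order of events is clear. Under Randomization and masking: "After the completion of the baseline assessment, eligible participants will be randomly allocated to two study groups". The sessions come afterwards. For the experimental arm, section (iii) Interventions says: "The PPI intervention includes eight weekly online groups (with 4-5 participants in a group) sessions". For the comparator, The control group says: "Participants in the control group will receive a video call (approximately 60 minutes each week for eight weeks". Participants know their arm.

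Two other analyses are planned separately in the Data analysis section: "Both intention-to-treat and per-protocol analyses will be performed", and "The generalized estimating equation will be used to assess the changes in the outcome measurements between groups over time, followed by contrast tests".

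Attendance is measured for acceptability, under Feasibility and acceptability, as "adherence rate: the number of PPI intervention sessions practiced divided by the total number of required sessions". That definition covers the PPI arm only. No definition of completion is given for the control arm.

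**The concern.** The sentence treats two different kinds of variable as one. Injury completeness is fixed before allocation, so within each of its levels the arms remain randomised. Completion happens after allocation and can depend on the arm, on the participant's mood and pain, and on how the intervention is received.

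The protocol itself supplies a link to prognosis. Its Introduction associates negative emotion and low self-efficacy with less engagement in physical activity, and says depression interferes with taking part in daily life. Depression is a primary outcome and exercise efficacy a secondary one. Completers and non-completers may therefore differ on what is being measured, whatever the treatment does.

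The arms also ask for different things. PPI involves group sessions, exercise and daily mindfulness practice; control involves a weekly call. There is no reason to expect the same people to finish in both. A completer contrast presented as a subgroup effect could show a difference where there is none, or hide a real one.

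**Working it through.** **Inputs from the protocol.** The target is "a widely acceptable sample size (i.e., 30 participants in each study group"), raised for 20% attrition to 36 per group; 30 x 1.20 = 36 reproduces that figure. The point does not rest on it. The protocol gives no completion rate by arm and no prognostic gap between completers and non-completers, so both are assumed below.

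**Formula.** Let p be the proportion completing in an arm, delta the mean advantage of completers over non-completers in SD, and m the arm mean. Since m = p x (completer mean) + (1 - p) x (non-completer mean):

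- completer mean = m + (1 - p) x delta
- non-completer mean = m - p x delta

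With no true effect, m is the same in both arms. If delta is also the same in both:

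- completers, PPI minus control = (1 - p_PPI) x delta - (1 - p_control) x delta = (p_control - p_PPI) x delta
- non-completers, PPI minus control = -p_PPI x delta + p_control x delta, the same quantity
- PPI completers minus all controls = (1 - p_PPI) x delta

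**Results (SD units; positive favours PPI).**

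| Contrast | Completion PPI / control | Multiplier | delta 0.3 | delta 0.5 | delta 0.8 |
|---|---|---|---|---|---|
| Completers | 80% / 80% | 0 | 0 | 0 | 0 |
| Completers | 70% / 90% | 0.2 | +0.06 | +0.10 | +0.16 |
| Completers | 90% / 70% | -0.2 | -0.06 | -0.10 | -0.16 |
| PPI completers v all controls | 70% / not used | 0.3 | +0.09 | +0.15 | +0.24 |

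**Equal rates are not enough if selection differs by arm.** Take 80% in both arms, delta = 0.5 in PPI and 0 in control. Completers: 0.2 x 0.5 - 0.2 x 0 = +0.10. Non-completers: -0.8 x 0.5 + 0.8 x 0 = -0.40. The signs reverse if the dependence is in the control arm instead.

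**Simulation check.** The true effect is null, the outcome is standard normal, and completion is a threshold on a latent variable correlated rho with the outcome.

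| Scenario | rho | Completers | Non-completers |
|---|---|---|---|
| 80% / 80%, related to outcome in PPI only | 0.3 | +0.10 | -0.42 |
| same | 0.5 | +0.18 | -0.70 |
| 70% / 90%, same rho in both arms | 0.3 | +0.09 | +0.18 |
| same | 0.5 | +0.15 | +0.30 |

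The comparison of all randomised participants gave a difference of 0.00 in every scenario. With 36 per arm and rho = 0.5, the two-sided type I error of the completer comparison was 9.9% (80% / 80%, PPI only) and 8.6% (70% / 90%). It was 5.0% when rates and mechanism were identical in both arms.

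**Precision.** At 70% / 90% there would be 36 x 0.7 = 25.2 and 36 x 0.9 = 32.4 completers. The standard error is about sqrt(1/25 + 1/32) = 0.27 SD. If non-completion ran at 20%, non-completers would number 36 x 0.2 = 7.2 per arm.

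**The case against.** The strongest reply is that this is one example in one sentence of a pilot about feasibility and preliminary effects. Intention-to-treat and a between-group longitudinal model are already planned, and no hypothesis or sample size rests on the completion split. That stands, and it limits the seriousness.

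Several stronger readings are tempting, and the protocol does not support them.

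- *The result will be biased in favour of PPI.* This needs an assumed completion pattern such as 70% / 90%. The one figure given, 20% attrition, is not split by arm. With a common delta, equal rates give zero and reversed rates give the opposite sign. Bias is also zero if completion is unrelated to outcome.
- *Arms will be compared among completers.* The sentence does not say so. Adherence is defined for PPI only, so a split within PPI is an equally open reading. It would avoid the between-arm contrast, but it would be an observational comparison and not a treatment effect.
- *The completer estimate will size the main trial.* The protocol says effect sizes will inform a future trial, not that they come from this subgroup.
- *The adherence definition is part of the error.* It is a legitimate acceptability measure.

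The bias sizes in the completer rows of the formula table also lie within the sampling error of about 0.27 SD. That is a reason not to read much into such a contrast, not a defence of testing it.

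Leaving detail to an analysis plan does not answer the point either. The protocol positively names a post-randomisation variable as a subgroup factor.

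**Conclusion.** The point holds in a limited form. Completion is not a valid subgroup factor for a randomised comparison. A between-arm contrast within its levels is liable to bias whose sign and size cannot be known from the protocol, and a within-PPI contrast does not estimate a treatment effect.

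The illustrative range for the completer contrast is -0.16 to +0.16 SD, including zero, assuming no true effect, completion of 70% to 90% and a common completer advantage of 0.3 to 0.8 SD. Comparing PPI completers (70%) with all controls gives +0.09 to +0.24 SD under the same gap. All of these rest on assumed inputs.

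Severity is should-fix. The planned intention-to-treat analysis is unaffected, and so is the injury-completeness subgroup.

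**What to change.** In the Data analysis section, limit subgroup analysis to baseline factors such as injury completeness and remove completion/non-completion from the list. Report outcomes by completion descriptively, labelled non-randomised, without a between-arm test. State that the intention-to-treat analysis is the basis for conclusions and for the effect size used to plan the future trial. The adherence definition needs no change.

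A complier-average estimate is optional and exploratory only. It is not a simple replacement. It assumes that assignment to PPI does nothing for those classed as non-completers, yet they may attend some of the eight sessions and may use the exercise video and the mindfulness recordings. If it is reported, that exclusion restriction should be stated, and a wide interval should be expected.

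The per-protocol analysis, planned separately, may depend on similar post-randomisation behaviour and should be read with the same caution.

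The cost is a sentence or two of text and no extra data. What is lost is a significance test among completers that could not be interpreted as a randomised effect.

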This study **aims** to evaluate the feasibility, acceptability, and preliminary effects of an eight-week Physical-Psychological Integrative (PPI) online-group intervention on physical inactivity, depression, and chronic pain for people with SCI living in the community.

Research hypotheses: when compared with those the control group (online telephone didactic education), participants in the PPI intervention group will indicate significantly greater:

1. Improvements in *the minutes of performing the moderate-to-rigorous physical activity as well as the number of days they are physically active* for a total of at least 60 minutes or more per day at post-intervention, and 3-month follow-up;
2. Improvements *in depression and chronic pain* at post-intervention, and 3-month follow-up;
3. Improvements in *mindfulness skills and quality of life* at post-intervention, and 3-month follow-up.

c) Plan of investigation:

(i) Study method/design

An open-label, two-arm pilot RCT will be conducted to investigate the effects between the intervention (PPI online-group intervention) and the control group (brief online didactic education) for people with SCI living in the community over a 3-month follow-up. Qualitative interviews with focus groups involving participants in the PPI intervention group will be conducted post-intervention,

to explore participants' views about acceptance, strengths and limitations, and suggested improvements of the intervention. Participants' recruitment and other study procedures are summarized in a flow chart (Appendix 1) according to the CONSORT statement.

(ii) Participants (subjects)

Study participants will be recruited from the Hong Kong Direction Association for the Handicapped and other community centers in Hong Kong, where groups of people with physical impairments can be reached. The Hong Kong Direction Association for the Handicapped (<https://www.4limb.org/>) is a **typical non-government organization that serves a large group of people with severe physical impairment/handicaps in Hong Kong**. According to personal communication with the President of the Association, there are approximately a thousand members of the association and over 30% of them are SCI survivors. Emails/phone call invitations will be sent to potential participants and advertising posters will also be used to encourage them to participate.

Eligibility:

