**Primary outcomes include**

Leisure-time Physical Activity. Participants' leisure-time moderated-to-rigorous physical activity will be assessed by using the Fitbit Orb (San Francisco, IL) which is a wearable, display, triaxial accelerometer that pairs with Bluetooth with compatible smartphones. It can monitor the heartbeat rate of users for each minute. Participants will be asked to wear the Fitbit tracker for more than 10 hours a day (defined as daily adherence) throughout the study period. This accelerometer-based wristband activity tracker has shown its validity in measuring physical activity in cohorts with SCI [26].

Depression. The 9-item Patient Health Questionnaire will be used to measure the participants' depression level. Participants will be asked to rate "how often they were bothered by specific symptoms over the last two weeks" with each item rating from 0 (not at all) to 3 (nearly every day). Higher scores indicate greater symptoms of depression. The scale has indicated satisfactory reliability in the SCI population [16].

Chronic Pain. An 11-point numerical pain rating scale will be used to access pain intensity (in the past week), where zero means no pain and 10 means the worst imaginable pain. The scale has demonstrated good reliability in the Chinese SCI population [20].

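### A pilot sized for feasibility and estimation still frames its hypotheses as significance tests on three unranked primary outcomes at two time points, each at two-sided 0.05

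*Protocol*

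**What the plan says.** **Purpose and size.** The Sample size section takes 30 per group as a widely accepted figure "for a preliminary analysis to examine intervention feasibility and to estimate a between-group effect". It gives no power, target effect or standard deviation. Allowing for 20% attrition, it recruits 36 per group, 72 in total. The Preliminary effectiveness section says effect sizes and intervals will be used to size a later, fully powered trial.

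**Hypotheses.** Section b) states that "participants in the PPI intervention group will indicate significantly greater" improvements than controls. Hypothesis 1 concerns "the minutes of performing the moderate-to-rigorous physical activity as well as the number of days they are physically active", and Hypothesis 2 concerns depression and chronic pain. Each is to hold "at post-intervention, and 3-month follow-up".

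**Outcomes.** The list headed "Primary outcomes include" contains leisure-time physical activity, depression (PHQ-9) and pain (11-point rating). None is named as leading.

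**Tests.** Data analysis says: "The generalized estimating equation will be used to assess the changes in the outcome measurements between groups over time, followed by contrast tests". It then adds: "Level of significance is set at" p<0.05, two-tailed. The text does not say whether the contrasts depend on the overall test. Between-group Cohen's d is also planned there.

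**The concern.** The sample size section and the hypotheses ask different things of the same data. The first asks for an estimate with its uncertainty. The second asks for a significant or non-significant answer on several outcomes at two visits, with nothing in the text to say which answer matters.

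A team that follows the plan as written could report any one nominally significant contrast as an effect of PPI. The 5% level would not describe the error rate of that claim. At this sample size, a true moderate effect could also easily be non-significant and be read as absence of effect. At stake is what the pilot may legitimately say about preliminary effects.

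**Working it through.** **1. The plan's own figure.** 30 × 1.2 = 36 per group, 72 in total, as stated. After 20% loss, 36 × 0.8 = 28.8, so about 29 completers per arm.

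**2. Number of primary tests.** Three outcomes × two time points = 6. If activity is counted as minutes and active days, as in Hypothesis 1, there are four measures × two time points = 8.

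**3. Error under a full null, independent tests, any single win counted.** A two-tailed 0.05 test gives a false result favouring PPI with probability 0.025.

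| Tests | Either direction, 1 − 0.95^k | Favouring PPI, 1 − 0.975^k |
|---|---|---|
| 1 | 5% | 2.5% |
| 6 | 26.5% | 14.1% |
| 8 | 33.7% | 18.3% |

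**4. Correlated tests.** The protocol gives no correlations, so these are assumptions: 0 to 0.7 between outcomes and 0 to 0.8 between time points. Test statistics were simulated as multivariate normal, 400,000 draws per case.

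| Reading | Either direction | Favouring PPI |
|---|---|---|
| 6 tests, every contrast read | 16.5–26.5% | 8.2–14.1% |
| 8 tests, every contrast read | 19.5–33.7% | 9.8–18.3% |
| 6 or 8 tests, contrasts read only after a significant 2-df overall test for that outcome | about 8–18% | about 4–9% |

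The lowest figure favouring PPI is 4.0% (6 tests, gated, correlations 0.7 and 0.8). That is still above the 2.5% of one test.

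**5. What a non-significant result would mean.** Two-sample t-test, n = 29 per arm, two-sided 0.05; the effect size is an assumption.
- Power at d = 0.5: about 46%.
- d needed for 80% power: about 0.75.
- Approximate half-width of the 95% interval for d near zero: 1.96 × √(2/29) = 0.51.

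**6. Cost of Holm, if used.** At its strictest step the level is 0.05/3 = 0.0167. The same t-test then needs d of about 0.87 for 80% power, and power at d = 0.5 falls to about 30%.

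**The case against.** **Wrong quantity.** A reader might take 26–34% as the chance of a false efficacy claim. It is not: those figures include results favouring control. The hypotheses are directional, so the relevant figures are 14–18% if independent, against 2.5%. This objection stands. The upper end of each range also needs activity counted twice, although the primary outcome list has it once.

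**No stated win rule.** Each hypothesis is worded conjunctively: minutes as well as days, depression and pain, one time point and the other. If every component had to succeed, error within a hypothesis would not be inflated. The contrasts may also be meant to follow a significant overall test. Both readings are possible. The protocol fixes neither, so the figures are conditional on the any-one-wins reading.

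**It is only a pilot.** A reader might infer that the trial is presented as confirmatory, or that p-values decide whether a full trial goes ahead. The text supports neither. It speaks of preliminary effects, has no progression rule based on significance, and says that effect sizes and intervals will size the later trial.

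**A matter for the SAP.** Multiplicity adjustment and ranking are often left to a SAP, which is not at hand, so their absence alone is no fault. But the protocol itself states the significance-based hypotheses and the 0.05 rule. A SAP could add a hierarchy; it would not give this sample a power basis for those hypotheses.

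**Conclusion.** The point holds as a mismatch between a design meant for estimation and hypotheses decided by significance. If any single significant contrast is read as an effect, the chance of a false result favouring PPI under a full null is about 14% (6 tests) to 18% (8 tests) with independent tests. It is about 8–18% over the assumed correlations and about 4–9% if contrasts are gated by an overall test. One test gives 2.5%. These sizes rest on the any-one-wins reading and on correlations that the protocol does not supply. In the other direction, power of about 46% at an assumed d of 0.5 means that a non-significant result is weak evidence of no effect. The change should be made, because it alters what the trial can conclude and needs only wording.

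**What to change.** In section b) and in Data analysis:

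- Replace the prediction of significantly greater improvement with estimation of between-group differences and Cohen's d, each with a 95% confidence interval. The Preliminary effectiveness and Data analysis sections already plan effect sizes and intervals.
- Name one primary time point, for example post-intervention. Treat the other time point and "the number of days they are physically active" as supportive.
- State that no efficacy conclusion rests on p<0.05.
- Only if the sponsor keeps significance testing: apply Holm across the three primary outcomes at the named time point.

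**Cost.** Recruitment, assessments and interventions do not change. The sponsor can no longer present a single nominal p<0.05 as evidence of efficacy. Holm, if used, lowers power per outcome, at most by the amount shown for its strictest step.
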